### Statistical analysis

Continuous variables are described as mean ± standard deviation (SD) or median [interquartile range (IQR)] and are compared using the *t*-test or Mann-Whitney U-test. Categorical variables are expressed as percentages and compared using the Pearson χ^2^-test or Fisher's exact test, as appropriate. A univariate analysis is expected and adjustment is scheduled according to the success or not of recanalization. Primary outcome is analyzed in intention-to-treat, safety outcomes in per-protocol.

No intermediate analysis is planned. All data for the primary outcome will be assessed at the end of the study. The inclusion of 50 patients is planned over 30 months. This sample will allow to evaluate the feasibility of tDCS in the very acute phase of stroke and should highlight a tendency which will be used in further studies to demonstrate a statistically significant infarct growth difference between the two groups.

The number of patients (*n* = 25 per group) was empirically chosen to match the recruitment capacity of our center during the study period, and because we believe it would provide a reliable estimate of the effect size of the intervention for further studies. This planned number of patients was not based on a formal sample size calculation and we are aware that the present pilot trial will most likely be underpowered to demonstrate the superiority of the intervention over the control group with regard to the primary outcome.

In order to inform sample size and power calculations, we have used unpublished data from 200 consecutive patients who underwent mechanical thrombectomy for acute ischemic stroke in our institution and for whom infarct growth between admission and 24 h follow-up imaging was estimated using the method described in section Primary Outcome (voxel-wise infarct growth on DWI). These data were used to confirm the log-normal distribution of infarct growth and to provide the expected median and SD for the control group of STICA, namely 16 and 48.8 ml, respectively. Using the method described by O'Keeffe et al. (41), and assuming a 30% relative reduction in median infarct growth in the treatment group, 177 patients per group would be needed (two-sided comparison of untransformed medians, alpha = 5%, beta = 20%). Based on this effect size, a sample size of 25 patients per group would yield a statistical power of 18%. Conversely, with 25 patients per group, the effect size that could be detected with a statistical power equal to 80% would be a 65% relative reduction in infarct growth. Such an effect size may seem overly optimistic but the main aim of this pilot study is to provide a reasonable estimate of infarct growth reduction with cathodal tDCS, in order to inform the sample size calculation for, and feasibility of a multicenter phase IIb or phase III superiority trial.

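### The primary comparison is left open between two tests, with no baseline covariate and no ratio estimate, although the trial plans on a log-normal outcome and aims to estimate a relative reduction

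*Protocol article*

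**What the plan says.** All of this is in the protocol article. Its Statistical analysis section gives one rule for every continuous variable: they are summarised by mean and SD or by median and IQR, and "are compared using the *t*-test or Mann-Whitney U-test". It adds: "A univariate analysis is expected and adjustment is scheduled according to the success or not of recanalization". No transformation, baseline covariate or effect measure is named for infarct growth.

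The sample-size text in the same section uses 200 local thrombectomy patients. "These data were used to confirm the log-normal distribution of infarct growth", and they supply the "expected median and SD for the control group of STICA, namely 16 and 48.8 ml, respectively". The calculation proceeds by "assuming a 30% relative reduction in median infarct growth in the treatment group", from which "177 patients per group would be needed"; the comparison is labelled "two-sided comparison of untransformed medians, alpha = 5%, beta = 20"%. At 25 per group the article gives 18% power, and a 65% reduction as detectable with 80% power. It says that "The number of patients (*n* = 25 per group) was empirically chosen", that the trial is probably underpowered, and that its main aim is a reasonable estimate of the reduction in infarct growth for planning a larger trial.

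The Primary outcome section shows that the lesion on the admission DWI is segmented as part of measuring the outcome. Under Secondary outcomes, recanalization is assessed after arteriography or by MR angiography at day 1.

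**The concern.** The named tests do not match the planning model or the aim. A t-test on millilitres compares means, whereas the planning is in medians. Mann-Whitney tests a shift in ranks and, as written, comes without an estimate. Neither delivers the relative reduction, with its interval, that the next trial is to be sized from.

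The two tests can also point to different sizes of effect, so leaving the choice open leaves the primary quantity open. The one scheduled adjuster is largely fixed after treatment has begun. Baseline DWI volume, measured before randomisation, is not used. Allocation is described as blocked, with no stratification mentioned, and two amendments widened the population. Chance imbalance is therefore a real possibility with 25 per arm.

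**Working it through.** **Inputs.** Control median 16 ml, SD 48.8 ml, log-normal growth, two-sided 5%, 80% power, reduction in the median of 30% or 65%, 25 per group (all from Statistical analysis).

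**Log-scale variance.** For a log-normal variable, s² = ln[(1 + √(1 + 4(SD/median)²))/2].
- Control: SD/median = 48.8/16 = 3.05, so s² = 1.278 (log-SD 1.131).
- Active, 30% reduction: median 11.2 ml, SD kept at 48.8 ml, s² = 1.586.
- Active, 65% reduction: median 5.6 ml, SD kept at 48.8 ml, s² = 2.222.

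**Reproducing the plan.** n = (1.960 + 0.842)² × (s²control + s²active) / (ln ratio)².
- 30% reduction: 7.849 × 2.865 / 0.3567² = 176.7, that is 177.
- Power at 25 per group: Φ(0.3567/√(2.865/25) − 1.96) = Φ(1.054 − 1.96) = 18.2%.
- 65% reduction: Φ(1.0498/√(3.501/25) − 1.96) = Φ(2.806 − 1.96) = 80.1%.

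All three figures agree. The alternatives tried do not give all three:
- Equal log-SD in both arms gives 158 per group and 19.9% power.
- A delta-method comparison of untransformed medians gives 179 per group with equal raw SD, or 166 with equal log-SD. It then needs 29 or 27 per group at a 65% reduction, not 25.

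**Power of the candidate tests.** Simulation with 25 per group and 20,000 trials per scenario:

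| Scenario | Raw t | Mann-Whitney | Log-scale t (Welch) |
|---|---|---|---|
| 30%, SD 48.8 ml in both arms | 7.8% | 16.5% | 17.6% |
| 65%, SD 48.8 ml in both arms | 32.6% | 75.2% | 77.8% |
| 30%, equal log-SD | 12.2% | 17.9% | 19.2% |
| 65%, equal log-SD | 67.2% | 87.2% | 89.2% |

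The first two rows are the plan's own model. Repeat runs with other seeds move these figures by up to about one percentage point.

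**Why the t-test differs.** The log-normal mean is median × exp(s²/2). Control: 16 × exp(0.639) = 30.3 ml. Active at a 30% reduction: 11.2 × exp(0.793) = 24.8 ml. A 30% fall in the median is then an 18% fall in the mean (24.8/30.3 = 0.82). At 65% the active mean is 17.0 ml, a 44% fall.

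**Baseline adjustment.** The article gives no correlation between baseline volume and growth, so 0.3, 0.5 and 0.7 are assumed.
- Power of a log-scale ANCOVA at a 30% reduction, plan's model: 18.6%, 21.8% and 29.7%, against 17.6% unadjusted.
- 95% CI factor for the ratio, equal log-SD: exp(1.96 × √(2 × 1.278 × (1 − r²)/25)) = 1.87 unadjusted, then 1.82, 1.72 and 1.56.
- Around an estimate of 0.70 that is 0.37 to 1.31 unadjusted (0.70/1.87 to 0.70 × 1.87), and 0.45 to 1.10 at r = 0.7.

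**Zero growth.** Voxel-wise growth can be zero, so a log analysis needs a rule. Adding 1 mL to every value turns a true ratio of 0.70 into about 0.73–0.74, and 0.35 into about 0.41–0.43.

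**The case against.** Several stronger readings are tempting, and the article does not support them.

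- A reader might infer that the primary comparison is unadjusted. It is not: adjustment for recanalization is scheduled. What is missing is a covariate known before randomisation.
- A reader might infer that both tests waste power by working on the raw scale. Mann-Whitney uses ranks and is unchanged by a log transform. It loses only one to three points against the log-scale t-test.
- A reader might infer that the raw t-test will be used. The rule is generic, and the sample-size text speaks of medians and log-normality, so Mann-Whitney is the more natural reading for infarct growth. A full analysis plan may settle it.
- The raw t-test's shortfall depends on the variance model. With equal log-SD its power at a 65% reduction is about 67–68%, not 33%. Part of the shortfall reflects a different target (means, not medians).

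It can also be said that covariates and effect measures are often left to the analysis plan, that the sample was not formally sized, and that the best adjusted interval above still includes 1.

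All of that stands and limits the size of the point. It does not remove the mismatch within one section of the article: its planning figures come from a log-scale comparison that it does not name as the analysis, and its aim is an estimate that neither named test, as written, supplies.

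**Conclusion.** The point holds as an unfixed and poorly matched primary analysis. It is not an error in the planning figures, which reproduce. The large power loss is confined to the raw t-test option: about 8% instead of 18% at a 30% reduction, and 33% instead of 80% at a 65% reduction, if the SD is 48.8 ml in both arms. If Mann-Whitney is used, power is near the stated level and the defect is the missing ratio and interval.

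The benefit of using baseline volume is certain in direction only if that volume predicts growth. Its size is an assumption, from about one to twelve percentage points of power over correlations of 0.3 to 0.7. Because the trial declares itself underpowered for a test, the estimate and its interval are its main product, and that is where the gap matters.

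**What to change.** Before unblinding, name one primary analysis in the analysis plan:

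- A linear model on log infarct growth with arm and log baseline DWI volume. Other covariates known before randomisation, such as admission NIHSS, may be added.
- The adjusted active/sham ratio with its 95% CI as the primary estimate.
- A small offset or other rule for zero growth, fixed in advance, with a sensitivity check. The 1 mL result shows that the offset can pull the ratio towards 1.
- Mann-Whitney as the sensitivity analysis, and no raw-scale t-test for the primary outcome.
- Any analysis by recanalization success kept apart from the primary estimate, since that status is largely determined after randomisation.

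The cost is wording, the need to fix the rule for zeros, and one or two degrees of freedom. No new patients or measurements are needed.

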#### Secondary outcomes

We defined two secondary clinical outcomes, a safety outcome and three subgroups analyses.

NIHSS: a neurological exam (with NIHSS score) is assessed at the admission and at 7 days or discharge if earlier. The difference between NIHSS score at day 7 (or discharge if earlier) and on admission constitutes the first clinical outcome assessment.Modified Rankin scale (mRs): the mRs is a 7-point disability scale ranging from 0 (no symptom) to 6 (death).The mRs is estimated at 3 months by phone interview using a simplified and standardized questionnaire (33). Whenever possible, the patient will be interviewed directly. If the patient is unable to complete the interview, the interview will be conducted based on information from the relatives or the patient's general practitioner. The mRs at 3 months constitutes the second clinical outcome assessment.

Safety outcome: safety variables, including major adverse effects (neurologic deterioration) and minor adverse effects (itching sensations, cutaneous rash, headaches, vertigo, nausea) are monitored during tDCS stimulation, and then again at day 1 and day 2.Subgroup analyses are planned according to the following stratifications: (i) patients with and without perfusion–diffusion mismatch, with hypoperfusion defined as *T*_max_ > 6 s, on admission MRI. The perfusion–diffusion mismatch is defined by the volumetric ratio between perfusion lesion (at *T*_max_ > 6 s) and diffusion lesion (ratio > 1.8). The mismatch as defined is a neuroradiological marker of the ischemic penumbra, the target of our protocol; (ii) patients with NIHSS admission score above vs. below the median NIHSS admission score; (iii) presence or absence of arterial recanalization measured by the thrombolysis in cerebral infarction scale (TICI) post-arteriography or by MR Angiography at day 1 (successful recanalization on arteriography is estimated by a TICI scale 2b or 3) and (iv) patients with and without initial large vessel occlusion. The patient population will be clearly described with respect to vessel occlusion (no vessel occlusion, otherwise site of occlusion) in further publication.

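### The 3-month mRS has no named ordered analysis and no adjustment for admission NIHSS; the only adjuster planned is recanalization, which is observed after randomisation

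*Protocol article*

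**What the plan says.** **Outcome.** The Secondary outcomes section of the protocol article says that "the mRs is a 7-point disability scale ranging from 0 (no symptom) to 6 (death"), and that "The mRs at 3 months constitutes the second clinical outcome assessment". It gives no variable type, cut-point or test for it.

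**Tests.** The Statistical analysis section has two generic rules. Continuous variables are compared by t-test or Mann-Whitney U-test. For the other kind, "Categorical variables are expressed as percentages and compared using the Pearson" chi-square or Fisher's exact test. The mRS is assigned to neither rule.

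**Adjustment.** The analysis is to be univariate, and "adjustment is scheduled according to the success or not of recanalization". The sentence is not tied to a particular outcome. Under Secondary outcomes, recanalization is read from the TICI scale after arteriography or from MR angiography at day 1. Under Randomization and Intervention, the code is opened before revascularization whenever possible, otherwise during it, and stimulation starts as soon as possible after inclusion.

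**Baseline severity.** NIHSS is assessed at admission. It is used for the change score to day 7 (or discharge) and for a subgroup split at the median. It is not named as an adjuster.

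**Size.** "The number of patients (*n* = 25 per group) was empirically chosen to match the recruitment capacity of our center". The article says openly that the trial is probably underpowered.

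**The concern.** The mRS is ordered, and the trial's hypothesis is directional: less infarct growth should move patients towards better grades. A chi-square or Fisher test on seven unordered categories cannot tell such a shift from any other difference in shape, and it gives no single effect measure. With 25 patients over 7 levels the average count is 25/7 = 3.6 per cell, so the table is also sparse.

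The choice of adjuster is a separate matter. Admission severity may vary widely, because the amendments opened inclusion irrespective of NIHSS score, and chance imbalance is a real risk with 25 per group. Recanalization is observed after randomisation and usually after stimulation has begun. If stimulation affected it, adjusting for it would change the treatment comparison.

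At stake is how much a pilot, justified by what it can pass on to a later trial, learns from its functional scale at 3 months.

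**Working it through.** **1. The plan's own power figures, as a check on the inputs.** They concern infarct growth; none is given for the mRS.

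Inputs from Statistical analysis: "the expected median and SD for the control group of STICA, namely 16 and 48.8 ml, respectively"; a treated median 30% lower, for which the article states 177 per group; a two-sided 5% level and 80% power.

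- Log-scale variance from median m and raw SD: s² = ln[(1 + √(1 + 4(SD/m)²))/2].
- Control, m = 16: s² = 1.278. Treated, m = 0.7 × 16 = 11.2 with the same raw SD: s² = 1.586.
- n = (1.278 + 1.586)(1.960 + 0.842)² / [ln(16/11.2)]² = 176.7, so 177 per group, as stated.
- Power at 25 per group: 18.2% (stated 18%).
- A 65% reduction needs 24.9 per group for 80% power, as stated.

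The primary-outcome figures reproduce.

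**2. Assumptions for the mRS.** The documents supply none of these.

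- Control distribution with 46% at mRS 0-2. The Introduction quotes 46% with mild disability at 3 months; reading this as mRS 0-2 is an assumption. One distribution that fits is 12/18/16/14/18/8/14% for grades 0 to 6. Under it, the largest expected control count is 25 × 0.18 = 4.5, so every control cell is below 5.
- Proportional-odds treatment effect, with the odds ratio (OR) conditional on the baseline covariate.
- One normal baseline covariate standing in for NIHSS, with slope b on the latent logistic scale. Latent R2 = b²/(b² + π²/3). For b = 1.3 this is 1.69/(1.69 + 3.29) = 0.34; for b = 2.2 it is 4.84/(4.84 + 3.29) = 0.60.
- 25 per group, two-sided 5%, 2,500 simulated trials per scenario. The simulation standard error is at most √(0.25/2500) = 1 percentage point.
- Rank ANCOVA on the baseline covariate stands in for the adjusted ordinal regression.

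**3. Simulated power.**

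| Scenario | Chi-square, 7 levels | Fisher, 0-2 vs 3-6 | Chi-square, 0-2 vs 3-6 | Mann-Whitney | Adjusted rank analysis |
|---|---|---|---|---|---|
| OR 3, R2 0 | 25% | 37% | 50% | 57% | 56% |
| OR 3, R2 0.34 | 17% | 24% | 36% | 40% | 54% |
| OR 3, R2 0.60 | 11% | 15% | 23% | 25% | 50% |
| OR 2, R2 0.34 | 8% | 12% | 19% | 20% | 26% |

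An exact test on all 7 levels does slightly better than chi-square: 19% in the second row.

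**4. Share of the adjusted power kept.**

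- Chi-square on 7 levels, OR 3, R2 0.34: 16.5/53.6 = 0.31. Over ORs of 1.5 to 5 and three assumed control distributions it keeps 20% to 48%, except in one scenario (66%, at OR 5 with no prognostic covariate).
- Mann-Whitney, OR 3, R2 0.34: 39.6/53.6 = 0.74. Over all scenarios it keeps 50% to 100%, and 74% to 82% at R2 0.34 under the main distribution.
- Chi-square on 0-2 vs 3-6 keeps about 41% to 100%. It falls below half only with the very strong covariate.

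**5. Ordinal regression itself.** A separate simulation (600 trials per scenario, marginal OR about 2, assumed NIHSS-mRS rank correlation 0.43 to 0.59) gave about 33% to 44% for NIHSS-adjusted ordinal regression against 11% to 13% for the 7-level chi-square. Its likelihood-ratio test had a type I error of 6.5% to 7.5%, so part of that gain is not real power.

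**The case against.** A reader might infer that the mRS falls under the chi-square/Fisher rule, that nothing in the plan uses its order, and that more than half the power is therefore lost. The documents do not support this. The mRS is never classified, and the same paragraph offers Mann-Whitney, which uses order and is a common choice for a 0-6 score. The large loss belongs to one possible reading, all 7 levels as unordered categories, and not to the stated plan.

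Other objections carry weight:

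- The test for a secondary outcome may sit in a full protocol or analysis plan that is not shown. Its absence from an article is no fault in itself.
- The mRS is secondary in a pilot that aims mainly to estimate the reduction in infarct growth, and a rank test is a legitimate choice at this size.
- The recanalization sentence is not tied to the mRS. No document says that stimulation affects recanalization; if it does not, adjusting for it need not bias the comparison. The risk comes from its timing and is not a demonstrated bias.
- The median-NIHSS subgroup is not limited to one outcome, so baseline severity may enter the mRS analysis there.

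Two things remain. A median-split subgroup is not adjustment. And the adjustment that the article does schedule uses a post-randomisation variable while a severity score measured at admission is available. Even against Mann-Whitney, adjusting for a prognostic baseline score gains power, and the adjusted model gives an estimate that can be carried forward. Admitted low power does not answer the point about the estimate.

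**Conclusion.** The point stands as a cheap improvement, not as an error in the plan. The article leaves open which generic test applies to an ordered 7-level outcome, names no baseline adjuster, and schedules adjustment only for a variable seen after randomisation.

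The size depends on the reading. At an odds ratio of 3 and R2 of 0.34, power is about 17% with the 7-level chi-square, 40% with Mann-Whitney and 54% with an ordered, baseline-adjusted analysis. With no prognostic covariate, Mann-Whitney loses nothing (57% against 56%). All these figures rest on the assumed mRS distribution, effect size and covariate strength. None of the options gives high power at moderate effects, so the main gain is a directional effect estimate with an interval, adjusted for baseline severity.

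**What to change.** State that the 3-month mRS is compared over its full ordered range (0 to 6) by proportional-odds regression adjusted for admission NIHSS, and report a common odds ratio with 95% CI. Give Mann-Whitney as the unadjusted check and percentages per grade as description. Say that recanalization is not an adjuster in the treatment comparison for this outcome.

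The cost is analysis wording only, since admission NIHSS is already collected. There are two drawbacks. The proportional-odds assumption needs a rough check, which 25 per group can support only weakly. A permutation p-value is also advisable, because the likelihood-ratio test is slightly liberal at this size.

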#### Randomization

All patients are randomly assigned to receive either cathodal or sham-tDCS. The randomization list was previously established with a biostatistician (using the block method), allocating a different 5-digit code to each patient included, in a sealed envelope. All five-digit codes are pre-programmed into the tDCS device to deliver either active or sham tDCS and the randomization list was transmitted to the biostatistician to maintain the blinding of all experimenters. At the time of inclusion, just after the MRI scanning and before revascularization treatment whenever possible (otherwise, during the revascularization procedure), the experimenter opens the sealed envelope corresponding to the number of the patient being included and discovers its 5-digit code.

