#### Intervention

The intervention consists in cathodal tDCS by the DC-STIMULATOR PLUS (neuroConn, Ilmenau, Germany), a CE-certified medical device, programmed to deliver either active or sham-tDCS according to a randomization 5-digit code. tDCS or sham is started as soon as possible after the inclusion, in the stroke unit or in the angiosuite during thrombectomy, in addition to reperfusion therapies. The investigator sets the cathode facing the ischemic injury (C3 or C4 according to the 10–20 system) and the anode facing the contralateral supra-orbital area (Figure 1). Then, the experimenter enters the 5-digit randomization code in the device, which blindly determines whether cathodal or sham stimulation is to be delivered, without the experimenter knowing which. Delivery of stimulation is for 20 min. Over a period of 6 h, the experimenter restarts the device every hour with the same 5-digit randomization code for another 20 min. The device delivers 1.5 mA (with 30 s for ramping up and ramping down) of cathodal direct current through the two sponge coated electrodes (electrodes size: 5 × 7 cm^2^; Figure 2). Impedance quality is obtained using saline solution and conductive gel (Elefix paste®). The device automatically checks impedance values during all tDCS sessions. In the sham condition, the device delivers 98 s of current including 30 s for ramping at the beginning and end of each session, in order to keep the blinding procedure (Figure 3). Indeed, usually, subjects feel discomfort under the electrodes during only the first few seconds or minutes of tDCS stimulation (18, 34). The experimenter notes every significant event: time of stroke onset, time of hospital arrival, time of first MRI, time of IV thrombolysis, and/or endovascular recanalization, time of each tDCS session (Figure 4).

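### The only named adjustment, and subgroup (iii), use recanalization success, which is observed after stimulation starts and has no stated value for patients without an occlusion

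*Protocol article*

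**What the plan says.** All references are to the protocol article.

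- **Adjustment** (Statistical analysis): "A univariate analysis is expected and adjustment is scheduled according to the success or not of recanalization". No other covariate is named. The same paragraph sets intention-to-treat for the primary outcome and lists the t-test and Mann-Whitney test.
- **Subgroup (iii)** (Secondary outcomes): "presence or absence of arterial recanalization measured by the thrombolysis in cerebral infarction scale (TICI) post-arteriography or by MR Angiography at day 1". It stands beside three subgroups defined on admission data: perfusion-diffusion mismatch, NIHSS and initial large vessel occlusion.
- **Success** (Secondary outcomes): "successful recanalization on arteriography is estimated by a TICI scale 2b or 3". No threshold is given for MR angiography.
- **Timing of allocation** (Randomization): "just after the MRI scanning and before revascularization treatment whenever possible (otherwise, during the revascularization procedure".
- **Timing of stimulation** (Intervention): "tDCS or sham is started as soon as possible after the inclusion, in the stroke unit or in the angiosuite during thrombectomy". Sessions are repeated hourly over 6 h.
- **Who is enrolled**: after the amendments, eligibility turns on being a candidate for a revascularization procedure, not on a visible occlusion (Inclusion and exclusion criteria). The population is to be described as "no vessel occlusion, otherwise site of occlusion" (Secondary outcomes).
- **Purpose** (Statistical analysis): the main aim is a reasonable estimate of the reduction in infarct growth, to size a later multicentre trial.

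**The concern.** A covariate fixed before randomisation can be adjusted for without changing what the treatment contrast means. Recanalization success is not such a covariate: it is read after active or sham current has been started. If the current has any influence on it, two things follow. Adjustment removes the part of the effect that runs through reperfusion. It also links treatment to any unmeasured factor that drives both recanalization and growth.

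Separately, a yes/no success variable has no natural value for a patient who had nothing to recanalize.

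This trial does not expect significance; its product is an effect estimate. The text plans both a univariate and an adjusted analysis without saying which leads, so the choice stays open until both are seen.

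**Working it through.** **1. Timing.**

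| Event | When |
|---|---|
| Admission DWI, angiographic sequence, NIHSS | Before randomisation |
| Randomisation | Before revascularization where possible, otherwise during it |
| Stimulation | As soon as possible after inclusion, then hourly over 6 h |
| Recanalization by TICI | After arteriography |
| Recanalization by MR angiography | Day 1 |
| Primary outcome DWI | Day 1 |

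On both routes recanalization is observed after treatment starts. On the MR angiography route it is read on the same day as the outcome.

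**2. Classification.** An occluded patient scored on arteriography has a defined value. An occluded patient scored on MR angiography has a named instrument but no stated threshold. A patient without occlusion has no stated value.

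**3. The plan's own figures, reproduced.** Inputs: control median 16 ml, SD 48.8 ml in both arms, log-normal growth, two-sided 5%, 80% power.

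- Log variance: s² = ln{[1 + √(1 + 4(SD/median)²)]/2}. Control: 1.278 (log-SD 1.131). Treated median 11.2 ml: 1.586.
- n per group = (1.278 + 1.586)(1.960 + 0.842)²/(ln 0.70)² = 176.7, so 177 as stated.
- Power at 25 per group = Φ(0.357/√(2.865/25) − 1.960) = Φ(−0.906) = 18.2%; stated 18%.
- Power for a 65% reduction = 80.1%; stated 80%.

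These figures are not in dispute.

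**4. Part of the effect adjusted away.** If recanalization divides median growth by k and tDCS raises the recanalization rate by Δp, the pathway ratio is exp(−Δp × ln k). Both inputs are assumptions.

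- Δp = 0.05, k = 2: 0.97
- Δp = 0.10, k = 3: 0.90
- Δp = 0.15, k = 5: 0.79

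The middle case is 0.110/0.357 = 31% of the assumed effect on the log scale. If tDCS lowers recanalization, the direction reverses.

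**5. Bias from an unmeasured factor.** Large-sample simulation (2,000,000 patients), regression on log growth. Assumed inputs: 70% recanalization on sham; recanalization effect −0.8 and unmeasured prognostic factor −0.6 per SD on log growth; the same factor raises the log-odds of recanalization by 1.0 per SD; direct tDCS ratio 0.70 or 1.00.

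| Rise in recanalization | Total ratio (direct 0.70) | Adjusted | Total ratio (no direct effect) | Adjusted |
|---|---|---|---|---|
| 0 points | 0.70 | 0.70 | 1.00 | 1.00 |
| 5 points | 0.67 | 0.72 | 0.96 | 1.03 |
| 10 points | 0.65 | 0.74 | 0.92 | 1.05 |
| 20 points | 0.60 | 0.78 | 0.85 | 1.11 |

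With no shift in recanalization, the two estimates agree even though the unmeasured factor is present. When the unmeasured factor does not drive recanalization, the adjusted ratio stays at the direct effect (0.70 or 1.00).

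**6. Unclassifiable patients.** If 10% or 20% had no occlusion (assumption) and were left out of the adjusted model, 45 or 40 of 50 would remain. Power for a 30% reduction would go from 18% to 17% or 15%, and for a 65% reduction from 80% to 76% or 71%.

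**7. Baseline covariates instead.** If they explain R² = 0.2 or 0.4 of log-growth variance (assumption), the 95% CI factor exp(1.96 × √(2 × 1.278 × (1 − R²)/25)) narrows from 1.87 to 1.75 or 1.62. With the plan's own unequal log variances, power for a 30% reduction becomes Φ(0.357/√(2.865 × 0.8/25) − 1.960) = 22%, or with 0.6 in place of 0.8, 27%.

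**The case against.** **The bias is conditional.** Severity driving both recanalization and growth is not enough; tDCS must itself change recanalization. The stated mechanism is protection of the penumbra until reperfusion, reperfusion therapy is usual care in both arms, and a device code blinds allocation, so different procedural handling is not expected. This stands: a reader might infer that the adjusted estimate is certainly biased, and the documents do not support that. They neither claim nor exclude an effect on recanalization.

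**An unadjusted comparison is retained.** The univariate analysis is in the same sentence, and the sample-size reasoning compares untransformed medians without covariates. A reader might infer that the adjusted estimate will size the next trial; no section says so. What remains is that the text does not rank the two.

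**Nobody is stated to be excluded.** A reader might infer that patients without occlusion are dropped, against intention-to-treat. The article does not say this, and their coding may be settled in an analysis plan not shown. What remains is that the chosen variable has no natural value for them.

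**Not naming baseline covariates is no error** in a condensed article, and the precision gain is modest in a trial that calls itself underpowered. This also stands; baseline covariates enter here as the replacement, not as an omission.

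The objection does not reach the choice itself: adjusting for a variable observed after treatment starts is fixed in the text.

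**Conclusion.** The point holds in a limited form. The only covariate adjustment named, and subgroup (iii), rest on a variable observed after randomisation and after stimulation starts. It is measured by two instruments at two times and has no stated value for a group of patients the protocol expects.

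If tDCS affects recanalization, the adjusted result does not estimate the total randomised effect and can mislead. Under the assumptions in the working, the distortion runs from negligible to a reversal of direction. If tDCS has no such effect, adjustment is unbiased and may gain precision, and only the classification problem remains. None of the distortion or patient-loss figures comes from the documents; they show scale only.

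This should be fixed rather than must be fixed, because an unadjusted comparison is also planned and the harm is conditional. It still deserves action: the estimate is what the trial is for, and the text leaves open which one leads.

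**What to change.** - Name one main result: the intention-to-treat comparison of log infarct growth, adjusted only for baseline variables already collected. These are log baseline DWI volume and baseline occlusion status or site, with admission NIHSS if 50 patients can carry a third covariate. Report the unadjusted comparison beside it.
- Move the recanalization-adjusted analysis to a labelled exploratory analysis, with no occlusion at baseline as its own level and a stated MR angiography definition.
- Report recanalization by arm, so that readers can judge whether tDCS may have altered it.
- Label subgroup (iii) post-randomisation and descriptive.

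Planned thrombectomy versus thrombolysis alone is left out: the Intervention section records times of treatments given, and nothing shows that a plan was recorded before randomisation.

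Cost: protocol or analysis-plan wording only; the admission MRI and clinical record already hold the covariates. The downside is that any precision gained from recanalization is kept only in the exploratory analysis.
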